#### Secondary outcomes

Secondary outcomes are (1) severity of delirium, (2) number of positive delirium assessment, (3) emergence agitation which is defined as RASS + 1 or more within 30 min after the endotracheal extubation, (4) delayed extubation (> 1 h after surgery), (5) perioperative adverse events including intraoperative awareness with recall or undesirable patient movement, bradycardia with the use of chronotropic agent, laryngeal spasm, bronchospasm, allergic reaction, arrhythmia, cardiac events (myocardial infarction, vasospasm, or cardiac arrest), or massive bleeding, (6) area under the mean blood pressure threshold (AUT), (7) quality of recovery using Qor-15 questionnaire (Stark et al. 2013), (8) postoperative nausea and vomiting (PONV), (9) incidence and severity of non-delirium complications (non-neurologic or neurologic) within 30 days after surgery, which are graded using Clavien-Dindo classification (Dindo et al. 2004; Landriel Ibañez et al. 2011), (10) length of hospital, defined as the number of days from index neurovascular surgery until initial hospital discharge and ICU stay, defined as the number of hours in the neurosurgical ICU following index neurovascular surgery until the initial ICU discharge, (11) changes in cognition. (12) The occurrence of fall-down and associated injury and functionality at 3 months after surgery.

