### Prespecified additional analyses and substudies

#### A. Comparing the incidence and severity of postoperative nausea and vomiting between the remimazolam-based TIVA and propofol-based TIVA

Neurosurgical patients are at high risk for the PONV (ref). Propofol-based TIVA in patients undergoing craniotomies has been associated with a lower incidence of PONV compared to inhalational anesthesia (Chui et al. 2014). Furthermore, a recent meta-analysis demonstrated that perioperative benzodiazepine administration reduced the risk of PONV (Au et al. 2024). In this regard, neurosurgical patients with multiple PONV risk factors are likely to benefit from remimazolam as the primary general anesthetic agent.

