### Statistical analysis

All reported study results except adverse events and non-delirium complications are analyzed, following the modified intention-to-treat-principle (ITT). Data will be descriptively presented using summary statistics such as median and quartiles, means and SD, or frequency and percent as appropriate. The standardized mean difference (SMD) will be used for the comparison of baseline data between the randomized groups. Acceptable covariate balance is defined as a standardized mean difference < 0.2 for the entire list of covariates. Repeated measurements, such as NRS score for pain and sleep quality, daily cumulative opioid requirement, and cognitive function will be compared using generalized estimating equation (GEE) analysis among groups.

For the analysis of primary outcome, we will employ a modified ITT principle, which means all randomized participants, regardless of protocol adherence will be included in the primary analysis, except for the case with surgery cancelation and withdrawal of consent after randomization. The incidence among groups will be compared by calculating the 95% CI of the incidence difference: incidence (remimazolam group)-incidence (propofol group), and noninferiority will be achieved if the upper limit of 95% CI is < 10%. The incidence of POD will be compared using a one-sided two-sample *z*-test with an alpha level of 0.025. We will use a multivariable logistic regression model, which will adjust the treatment effect for covariates found to be imbalanced between the two groups.

For the secondary outcome, except for the analysis of intraoperative adverse events and non-delirium complications in which the PP approach will be used, a modified ITT approach will be used. Group comparison will be performed using a two-sample *t* test or Mann–Whitney *U* test as appropriate for continuous variables, and a chi-square test or Fisher’s exact test for categorical variables. We will adjust the effect of imbalanced covariates using a multivariable logistic regression model for count variables and linear regression or quantile regression for continuous variables.

Subgroup analyses will be conducted to assess the consistency of differences in the primary outcome used to differentiate the effect of treatment among different populations (age, sex, surgery type, preoperative cognitive impairment, ASA physical status, duration of anesthesia, alcohol abuse, or preoperative benzodiazepine use within 24 h).

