A one-sided *P* value < 0.025 for the primary endpoint and a two-sided *P* value < 0.05 for the secondary endpoints will be considered statistically significant. Missing data will not be replaced, and interim analysis will not be performed. All statistical analyses will be performed by statistical experts utilizing SPSS, SAS, or R software.

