## Discussion

In this trial, we aimed to assess the non-inferiority of remimazolam, a new short-acting benzodiazepine, in terms of POD occurrence compared to the conventional intravenous anesthetics, propofol.

Remimazolam demonstrates a favorable pharmacokinetic and pharmacodynamic profile for general anesthesia. However, using benzodiazepines as the principal general anesthetic raises concerns among clinicians about the potential risk of increasing the incidence of POD. Sedation with benzodiazepines in the ICU has been associated with a higher incidence of delirium compared to non-benzodiazepines (dexmedetomidine, propofol) (Casault et al. 2021; Pandharipande et al. 2006; Zaal et al. 2015). Nevertheless, this evidence primarily stems from observational studies. Moreover, long-acting benzodiazepine drugs are more likely to increase the risk of POD compared to short-acting ones. Observational cohort studies have demonstrated no significant increase in the incidence of POD incidence with remimazolam as a general anesthetic in high-risk elderly populations compared to control groups (Aoki et al. 2023; Kaneko et al. 2023). In addition, a recent prospective randomized controlled trial involving 320 patients aged over 60 undergoing elective orthopedic surgery demonstrated a statistically insignificant difference in POD between remimazolam (15.6%) and propofol anesthesia (12.4%) (Yang et al. 2023). Meanwhile, patients in the remimazolam group experienced a lower incidence of post-induction hypotension and required fewer vasoactive drugs intraoperatively. Regarding the risk of POD, evidence from highly qualified randomized controlled trials is necessary for general anesthesia using remimazolam.

Confirming the study hypothesis would provide an opportunity to reappraise benzodiazepine as a principal anesthetic and broaden the options for intravenous anesthetics currently available. It could offer a rationale for adopting a novel drug anticipating several advantages over propofol. Conversely, rejection of the hypothesis would provide insights into potential side effects clinicians should consider when using the new drug.

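### Any secondary endpoint with two-sided P < 0.05 is to be called significant, across twelve multi-part outcomes with no hierarchy, gating, alpha control or exploratory label

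*Protocol article*

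**What the plan says.** The Statistical analysis section sets two thresholds. The first is "A one-sided *P* value < 0.025 for the primary endpoint", which belongs to a single non-inferiority comparison. The second covers everything listed as secondary: "a two-sided *P* value < 0.05 for the secondary endpoints will be considered statistically significant".

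The Secondary outcomes section numbers twelve items, and several hold more than one comparison. Examples are "5) perioperative adverse events including intraoperative awareness with recall or undesirable patient movement, bradycardia with the use of chronotropic agent, laryngeal spasm, bronchospasm" (the list continues), "10) length of hospital, defined as the number of days from index neurovascular surgery until initial hospital discharge and ICU stay" and "12) The occurrence of fall-down and associated injury and functionality at 3 months after surgery". Statistical analysis names the tests (t test or Mann–Whitney, chi-square or Fisher's exact, GEE for repeated measures). It gives no order of testing, no condition on the primary result, no adjustment and no exploratory label. No other section supplies one.

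**The concern.** A successful non-inferiority result would show only that remimazolam is not unacceptably worse than propofol on delirium. Any statement from this trial that remimazolam is better or worse on blood pressure, nausea and vomiting, recovery, length of stay or cognition would rest on the secondary outcomes. Under the stated rule, one chance result below 0.05 among them would carry the label statistically significant, as an advantage or as a harm. The rule gives a reader no way to separate such a result from a confirmatory one.

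**Working it through.** The plan states no family-wise error figure to reproduce. Its only figure for the secondaries is the per-test level of 0.05, two-sided.

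**Number of comparisons** (from Secondary outcomes)

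| Item | Low count | High count |
|---|---|---|
| 1–4: severity, positive assessments, agitation, delayed extubation | 4 | 4 |
| 5: adverse events, as one item or as nine event types | 1 | 9 |
| 6–8: blood pressure area, QoR-15, PONV | 3 | 3 |
| 9: complications, incidence and severity | 2 | 2 |
| 10: hospital and ICU stay | 2 | 2 |
| 11: cognition, one GEE analysis or two time points | 1 | 2 |
| 12: falls, injury, functionality | 3 | 3 |
| **Total** | **16** | **25** |

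One test per numbered item gives 12, the smallest reading. None of these counts includes the delirium subtypes (named as secondary in the Abstract), PONV severity, or the GEE comparisons of pain, sleep and opioid use.

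**Chance of at least one P < 0.05 if the drugs do not differ**

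For k independent tests the chance is 1 − 0.95^k:

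- k = 12: 1 − 0.540 = 0.460
- k = 16: 1 − 0.440 = 0.560
- k = 25: 1 − 0.277 = 0.723

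For normal test statistics with equal correlation ρ it is

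1 − ∫ [Φ((z − √ρ·u)/√(1−ρ)) − Φ((−z − √ρ·u)/√(1−ρ))]^k φ(u) du, with z = 1.96.

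The documents give no correlations, so ρ is an assumption:

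| k | ρ = 0 | ρ = 0.5 | ρ = 0.8 |
|---|---|---|---|
| 12 | 46% | 32% | 19% |
| 16 | 56% | 37% | 21% |
| 25 | 72% | 47% | 24% |

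If every test has full size 0.05, the expected number of false positives is 0.05k whatever the correlation: 0.6, 0.8 and 1.25.

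**Rare events.** Fisher's exact test uses less than its nominal 5% when events are few. With 330 per arm its exact size is 0.003 at an event rate of 0.5% and 0.014 at 1% (assumed rates). If 7 of the 25 comparisons add nothing, the independent-test figure is 1 − 0.95^18 = 60%. If 9 add nothing, it is 1 − 0.95^16 = 56%.

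**The case against.** **The gap may be filled elsewhere.** Data management refers to a predefined statistical plan and Data Availability to a full protocol; neither is shown. Ordering, gating and labelling are often left to such documents, so their absence alone would be no finding. That is right as far as it goes. But this article states the decision rule outright, and the end of Background says that it is meant as an advance record of the principal methods. A later plan that treated the secondaries as exploratory would have to override a published sentence.

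**A per-test threshold does not promise family-wise control.** This stands. Each test runs at 5% as stated, so it would be wrong to say that the plan exceeds its own error rate. The point is that the rule attaches the same word to every result, with no guide to how many chances it had.

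**The count of 25 is generous.** This largely stands. Nothing says that each event type in item 5 is tested separately. Many of these events may be rare, they are safety data for which multiplicity adjustment is not obviously helpful, and cognition falls under one GEE analysis. Hence 16 is shown beside 25.

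**Three stronger readings that a reader might infer are not supported:**

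- *A false secondary claim is more likely than not.* This holds only for the larger counts at low correlation. It fails for 12 tests even under independence (46%), and for 25 tests at correlation 0.5 (47%).
- *The investigators plan superiority claims from the secondaries.* The Discussion sentence "It could offer a rationale for adopting a novel drug anticipating several advantages over propofol" follows from confirming the delirium hypothesis, and the advantages it anticipates rest on earlier studies. The remark that "neurosurgical patients with multiple PONV risk factors are likely to benefit from remimazolam as the primary general anesthetic agent" is background to a substudy. Neither says what would be claimed if non-inferiority failed.
- *The subgroup analyses carry a similar error rate.* Their stated aim is "Subgroup analyses will be conducted to assess the consistency of differences in the primary outcome used to differentiate the effect of treatment among different populations". The significance sentence covers primary and secondary endpoints only, and no level is given for subgroups, so no error rate can be attached to them.

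**Conclusion.** The point holds in limited form. The document fixes a rule that calls any secondary result below 0.05 significant, over at least twelve tests, and nothing in it qualifies that rule. With no true differences, the chance of at least one such result runs from 19% (12 tests, correlation 0.8) to 72% (25 independent tests); the 16-test count gives 21–56%. These figures assume equal correlation and full test size, so rare events would pull them down. Nothing here touches the primary analysis. This is an inexpensive improvement in how secondary results are to be read, and it does not threaten the trial's main conclusion.

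**What to change.** Replace the clause on secondary endpoints in Statistical analysis with wording such as:

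> Only the primary non-inferiority test (one-sided 0.025) is confirmatory. Secondary outcomes are exploratory and will be reported as effect estimates with 95% CIs and nominal P values, unadjusted for multiplicity.

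Safety events should stay descriptive and unadjusted.

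If the sponsor wants a confirmatory secondary claim, it may name a short ordered list before unblinding and test it in that order at two-sided 0.05, only after non-inferiority has been shown. Whether to do so, and with which outcomes, is the sponsor's choice.

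The cost is a sentence or two before unblinding, with no extra patients, no new data and no change to the sample size. The one downside is that nominal secondary results can no longer be called statistically significant.

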## Discussion

In this trial, we aimed to assess the non-inferiority of remimazolam, a new short-acting benzodiazepine, in terms of POD occurrence compared to the conventional intravenous anesthetics, propofol.

Remimazolam demonstrates a favorable pharmacokinetic and pharmacodynamic profile for general anesthesia. However, using benzodiazepines as the principal general anesthetic raises concerns among clinicians about the potential risk of increasing the incidence of POD. Sedation with benzodiazepines in the ICU has been associated with a higher incidence of delirium compared to non-benzodiazepines (dexmedetomidine, propofol) (Casault et al. 2021; Pandharipande et al. 2006; Zaal et al. 2015). Nevertheless, this evidence primarily stems from observational studies. Moreover, long-acting benzodiazepine drugs are more likely to increase the risk of POD compared to short-acting ones. Observational cohort studies have demonstrated no significant increase in the incidence of POD incidence with remimazolam as a general anesthetic in high-risk elderly populations compared to control groups (Aoki et al. 2023; Kaneko et al. 2023). In addition, a recent prospective randomized controlled trial involving 320 patients aged over 60 undergoing elective orthopedic surgery demonstrated a statistically insignificant difference in POD between remimazolam (15.6%) and propofol anesthesia (12.4%) (Yang et al. 2023). Meanwhile, patients in the remimazolam group experienced a lower incidence of post-induction hypotension and required fewer vasoactive drugs intraoperatively. Regarding the risk of POD, evidence from highly qualified randomized controlled trials is necessary for general anesthesia using remimazolam.

Confirming the study hypothesis would provide an opportunity to reappraise benzodiazepine as a principal anesthetic and broaden the options for intravenous anesthetics currently available. It could offer a rationale for adopting a novel drug anticipating several advantages over propofol. Conversely, rejection of the hypothesis would provide insights into potential side effects clinicians should consider when using the new drug.

## Data Availability

Data sharing including the full protocol, individual participant and other relevant study data will be considered upon reasonable request. Only with the permission of the Data Review Board of Samsung Medical Center, the anonymized data will be available from the principal investigator ([name]).

## Abbreviations

3D-CAM: 3-Minute diagnostic interview for Confusion Assessment Method
ASA: American Society of Anesthesiologist
BIS: Bispectral index
CAM-ICU: Confusion Assessment Method for the Intensive Care Unit
CI: Confidence interval
CRF: Case Report Form
DMC: Data Monitoring Committee
DRS: Delirium rating scale
EEG: Electroencephalogram
ICU: Intensive care unit
IRB: Institutional Review Board
ITT: Intention to treat
MoCA: Montreal Cognitive Assessment
NRS: Numeric rating scale
POD: Postoperative delirium
PONV: Postoperative nausea and vomiting
PP: Per protocol
RASS: Richmond Agitation-Sedation Scale
SAEs: Serious adverse events
SD: Standard deviation
TCI: Target controlled infusion
